## **2.2 Study Endpoints**

### **2.2.1 Primary Endpoint**

The primary endpoint is initial parasitological cure at day 29 and is defined as absence of parasites in tissue aspirate at day 29.

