### 4.2. Exclusion criteria

The presence of any of the following will exclude a subject from study enrolment:

- Women of child-bearing potential (defined as women who have achieved menarche) who are not using an assured method of contraception or are unwilling to use an assured method of contraception for the duration of treatment and four months after.\*\*\*
- Pregnant women or breast-feeding mothers.
- Patients with grade 2 or 3 post kala-azar dermal leishmaniasis (PKDL) lesions
- Clinical symptoms of chronic underlying disease such as severe cardiac, renal or hepatic impairment.
- Known hypersensitivity to AmBisome® and/or miltefosine.
- Patients receiving allopurinol treatment

*\* Patients with a platelet count less than 40,000/  $\mu$ L or Hemoglobin (Hb) less than 5g/dL or not palpable spleen or bleeding tendency (e.g. epistaxis) should be diagnosed by bone marrow rather than spleen aspirate. Ideally, the same type of tissue aspirate should be performed at screening and at day 29 assessment (except if not clinically indicated). During follow up, a spleen aspirate can be performed, if required, provided there is recovery of the platelet count, Hemoglobin and/or bleeding tendency.*

*\*\* If the patient is illiterate an impartial witness should be present during the consenting procedure and should also sign.*

*\*\*\* Women who are sexually active and not using an assured method of contraception i.e. either IUCD, medroxyprogesterone acetate (Depo-Provera) but who wish to participate in the trial must sign an additional consent form and agree to receive a long-acting assured form of contraception. Oral contraceptives are not considered adequate in this context because of the high prevalence of vomiting and diarrhoea associated with miltefosine treatment. As these patients are HIV positive, the above contraceptive methods would be in addition to the use of condoms which should be normal practice and will be encouraged throughout the study.*

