| Secondary Prophylaxis                                                       |                     |                    |   |    |                |                                                   |                                                 |                 |                  |                  |
| Start                                                                       |                     |                    |   |    |                | x                                     |                                                 | x   |                  |                  |
| Glucose                                                      |                     |                    |   |    |                |                                                   |                                                 |                 |                  |                  |
| Urea, creatinine +
Liver function
(Bilirubin, AST, ALT)  |                     |                    |   |    |                |                                                   |                                                 |                 |                  |                  |
| Safety monitoring
(SAEs only)                                |                     |                    |   |    |                |                                                   |                                                 |                 |                  |                  |

- 1 Includes weight, height, (screening only) vital signs, VL clinical signs and symptoms.
- 2 Performed only when clinically indicated.
- 3 CD4 count not performed in case of extended treatment is needed.
- 4 Tissue aspirate: This will be a spleen aspirate; if the spleen is not palpable a bone marrow aspirate will be done
- 5 Ideally, the same type of tissue aspirate should be performed at screening and at day 29 assessment (except if not clinically indicated).
- 6 Dashed line arrow refers specifically to patients receiving an extended treatment. Solid-line arrow refers to patients cured at day 29 assessment.
- 7 For patients that are parasite negative at day 29 with CD4 count < 200 cells/mL and with no known contra-indication to Pentamidine. Patients need also to be available for the monthly follow-up visits to receive the secondary prophylaxis.

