### Laboratory assessment

Parasitological assessment will be done at baseline and at day 29; it will also be done at day 58 for patients who have an extended treatment. During the follow-up, it will only be performed when clinically indicated. It will be a spleen aspirate or a bone marrow aspirate if the spleen is not enlarged. Aspirates are smeared on slides, stained and graded according to the standard logarithmic criteria as defined in the below table:

| Count Oil Immersion x 100 |                                |
|---------------------------|--------------------------------|
| 6+                        | > 100 parasites per field      |
| 5+                        | 10-100 parasites per field     |
| 4+                        | 1-10 parasites per field       |
| 3+                        | 1-10 parasites per 10 fields   |
| 2+                        | 1-10 parasites per 100 fields  |
| 1+                        | 1-10 parasites per 1000 fields |
| 0                         | 0 parasite per field           |

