### **10.6. Efficacy Analysis**

The primary and secondary endpoints have been described in section 2.2.

The primary endpoint (day 29) analysis will be defined as follows:

- Treatment success: absence of parasites on day 29; hence no rescue medication provided up to this time-point.
- Treatment failure: presence of parasites at day 29 *or* requirement of rescue medication due to lack of clinical improvement/ response *or* withdrawn from the study (e.g. due to a treatment limiting adverse event/ patient absconded) *or* death.

The data will be analysed as proportions according to an intention to treat and per protocol analysis for each treatment arm.

The secondary endpoint (12 months post treatment) analysis will be defined as follows:

- Treatment success: treatment success at day 29 or at day 58 in case of extended treatment and patient being alive and disease free (absence of signs and symptoms of VL or if symptomatic, a negative parasitological assessment by tissue aspirate) at day 390.
- Treatment failure: presence of signs of symptoms of VL, confirmed by presence of parasites in a parasitological investigation. It is mandatory that all patients who have possible presence of the disease have a parasitological assessment (a spleen aspirate or a bone marrow aspirate if the spleen is not palpable).

The primary endpoint will be analyzed following Whitehead (1983) including point and interval estimation of the proportion cured in each treatment arm.

Additional analyses will be conducted to evaluate potential differences in response to treatment between relapse versus primary VL cases, and patients that have previous exposure to ART or not. This will be done at the final sequential analysis (when we reach 66 per arm) and after one year follow up. A detailed description will be included in the statistical analysis plan.

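### The aspirate-site rule in schedule footnote 4, 8.3 and 10.6 tests only the spleen and conflicts with the platelet, haemoglobin and bleeding limits in the 4.2 note; at day 29 those limits are not stated

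*Protocol*

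**What the plan says.** The protocol states the choice between spleen and bone marrow in several places.

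- **Section 4.2, note on diagnosis** (the synopsis carries a similar note). Patients with platelets below 40,000/µL, or haemoglobin below 5 g/dL, "or not palpable spleen or bleeding tendency (e.g. epistaxis) should be diagnosed by bone marrow rather than spleen aspirate". The note then asks for the same tissue at screening and day 29, with an exception. It ends by allowing a spleen aspirate during follow-up "provided there is recovery of the platelet count, Hemoglobin and/or bleeding tendency".
- **Section 5, footnote 4**, attached to the whole aspirate row: "Tissue aspirate: This will be a spleen aspirate; if the spleen is not palpable a bone marrow aspirate will be done".
- **Section 5, footnote 5**, attached to the day 29 cell: "Ideally, the same type of tissue aspirate should be performed at screening and at day 29 assessment (except if not clinically indicated").
- **Section 8.3, Laboratory assessment**: "Parasitological assessment will be done at baseline and at day 29", and on the site, "It will be a spleen aspirate or a bone marrow aspirate if the spleen is not enlarged".
- **Section 10.6**, for suspected disease at the 12-month endpoint: "a spleen aspirate or a bone marrow aspirate if the spleen is not palpable".
- **Section 9.2** asks that subjects withdrawn before the end of the course still have the day 29 parasitology, and waives it where it is contraindicated.

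The day 29 aspirate carries the primary endpoint, which section 2.2.1 gives as initial cure "defined as absence of parasites in tissue aspirate at day 29".

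**The concern.** The 4.2 note has four triggers for bone marrow: platelets, haemoglobin, a spleen that cannot be felt, and bleeding. Footnote 4, 8.3 and 10.6 each keep only the spleen finding, and none refers back to 4.2. A reader who works from the schedule, as site staff commonly do, meets a spleen-by-default rule without the blood-count and bleeding limits that the sponsor thought necessary.

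What is at stake is the safety of an invasive procedure in a population where, by the protocol's own background section, an enlarged spleen and pancytopenia are classical features of the disease. A palpable spleen together with low counts is therefore a foreseeable combination. Day 29 deserves particular attention because the aspirate is scheduled for every patient at that visit.

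**Working it through.** No figure in the plan needs reproducing. The check sets the rules side by side and follows a patient with a palpable, enlarged spleen who is below the platelet or haemoglobin limit, or is bleeding.

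| Visit | Footnote 4 / 8.3 / 10.6 | 4.2 note and other clauses | Result |
|---|---|---|---|
| Screening | Spleen (footnote 4, 8.3) | Bone marrow (4.2) | Direct contradiction |
| Day 29, marrow used at screening | Spleen (footnote 4, 8.3) | Same tissue preferred, so marrow (4.2, footnote 5) | The visit-specific text points to the safer site, but only as a preference |
| Day 29, spleen used at screening, newly low or bleeding, treatment completed | Spleen (footnote 4, 8.3) | Same tissue preferred, so spleen, unless not clinically indicated (4.2, footnote 5) | No limit stated; rests on the exception |
| Day 29, withdrawn before the end of the course | Spleen (footnote 4, 8.3) | As above, plus the contraindication waiver in 9.2 | Two general clauses; no limit stated |
| Later aspirates, low earlier | Spleen (footnote 4; 8.3; 10.6 for suspected disease) | Spleen only after recovery (4.2) | 4.2 gives the safer rule, but the other sections do not refer to it |
| Later aspirates, newly low | Spleen (footnote 4; 8.3; 10.6 for suspected disease) | The recovery sentence presupposes an earlier low value | No limit stated |

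Three readings of the text support the table.

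1. The limits in 4.2 are worded for diagnosis, so they do not by their terms extend to a test of cure.
2. The recovery sentence in 4.2 concerns follow-up. Section 8.3 lists the follow-up assessments as days 58, 86, 210 and 390, and the schedule gives day 29 its own column, so the sentence does not reach day 29.
3. The blood count needed to apply the limits is available. Full blood counts are scheduled at screening and on days 3, 10 and 29, and at day 58 for extended treatment. Nothing says that the day 29 result is read before the aspirate.

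**The case against.** The strongest reply is that day 29 is dealt with in the same paragraph that sets the limits. In the 4.2 note the same-tissue sentence and its exception come directly after the platelet, haemoglobin and bleeding criteria, so the natural content of the exception is those criteria. Footnote 5 repeats the exception on the day 29 cell itself, which makes it the visit-specific rule over the general footnote 4. Patients are in hospital and asked about adverse events every day to day 29 (8.7.3), so new bleeding should be noticed, and a blood count is due that day. This largely stands. It shows that a careful investigator would probably choose marrow. It does not remove the contradiction at screening, and it leaves the day 29 limits to inference when one cross-reference would state them.

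A reader might infer more: that the protocol orders a spleen puncture at day 29 in patients known to be unsafe for it, or that the decision would rest on a count 29 − 10 = 19 days old, taken before most new ART starts and before the monotherapy infusions of days 17 and 24 (2 × 5 = 10 of 40 mg/kg). The documents do not support either.

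- The exception releases the investigator from the spleen.
- The 19 days matter only if the count scheduled for day 29 is ignored.
- ART may start as late as four weeks (7.7), which is about day 28 and leaves almost no time for an effect.
- The protocol's statement on marrow suppression (8.6) concerns zidovudine combined with amphotericin B, while the standard starting regimen is tenofovir-based. Some patients use zidovudine, but no number is given.
- Counts may also rise on treatment.

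These figures describe timing and do not measure risk.

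**Conclusion.** The point holds as an inconsistency between stated rules for an invasive procedure. At screening, footnote 4 and 8.3 contradict 4.2. At day 29, and for patients newly low at later aspirates, the limits are absent and protection depends on general clauses that probably, but not expressly, mean the 4.2 limits.

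The size is small. The patients concerned at day 29 are those with a palpable spleen who had a spleen aspirate at screening and have since fallen below a limit or begun to bleed. The protocol gives no rate from which to count them. The omission itself is certain; its practical consequence is not. The conclusion assumes only that the limits the sponsor set for diagnosis are meant to protect the patient whenever the same procedure is repeated. It is a minor patient-safety harmonisation and changes no sample size, error rate or primary analysis.

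**What to change.** Make the 4.2 criteria the single aspirate-site rule and say that it applies at every aspirate, including day 29 and suspected relapse. Then:

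- replace the site wording in footnote 4, 8.3 and 10.6 with a reference to that rule;
- in footnote 5, and in the matching sentence of the 4.2 note and the synopsis, name the 4.2 limits as a case in which the same tissue is not clinically indicated;
- state that the blood count already scheduled at day 29 is seen before the aspirate.

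The clinical limits stay as the sponsor set them, and no new test is needed at day 29. At later visits where the count is done only on clinical indication, an aspirate would need a current count too.

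The cost is a wording amendment, a short wait for the count in patients who are already in hospital for about 30 days, and an occasional change of tissue between screening and day 29. The protocol already permits that change. It gives no detection rate by tissue, so recording the tissue used at each aspirate is enough to let the report show how often it happened.

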## 6. Enrolment procedures

A computer generated, randomization code will be used for patient treatment allocation to one of the two treatment arms. The randomization will be stratified according to the centre (i.e. Abdurafi and Gondar) as well as by whether or not VL occurred previously (i.e. primary and relapse case).

Two sets of individual, opaque, sealed and sequentially numbered envelopes will be provided to each trial site, one envelope per patient. One set will be used for primary VL cases and the second one for relapse patients.

Eligible patients who fulfill all the inclusion criteria and have none of the exclusion criteria, and from whom informed consent has been obtained, will be randomized to one of the treatment regimens using the sealed envelopes.

The investigator should open the lowest numbered envelope from the correct set (i.e. primary or relapse). The patient receives the treatment written on the card inside. The card must then be replaced in the envelope and retained for drug accountability and monitoring purposes. This method of treatment concealment will minimise selection bias as the investigator will not know the allocation of treatment for a specific patient until the envelope is opened.

## 7. Treatments

### 7.1. Investigational Product

**Name:** Liposomal Amphotericin B (AmBisome®)

**Class:** a macrocyclic, polyene antifungal antibiotic produced by *Streptomyces nodosus*.

**Mechanism of action:** affects sterol biosynthesis, disrupting the parasite membrane.

**Commercial source:** Gilead.

**Product appearance:** AmBisome® comes as a sterile lyophilised powder in a 15ml sterile Type 1 clear glass vial containing a yellow powder with the active ingredient amphotericin B 50mg encapsulated in liposomes. The closure consists of a butyl rubber stopper and aluminium ring seal with a removable plastic cap. Vials are packed in cartons of 10, with 10 filters provided.

**Administration:**

- Add 12ml of water for injection to each AmBisome® vial, to yield a preparation containing 4mg/ml (**do not use saline or any bacteriostatic agents**). AmBisome® is incompatible with saline and should not be mixed with other drug or electrolyte solution during administration.
- Immediately after the addition of water, shake the vials vigorously for 30 seconds to completely disperse the AmBisome®. Visually inspect the vials for particulate matter and continue shaking until complete dispersion is obtained.
- The infusion providing from 2.00 to 0.20mg of amphotericin per ml is obtained by dilution with 1 to 19 parts respectively, by volume of 5% dextrose injection.
- Withdraw the calculated volume of reconstituted AmBisome® into a sterile syringe.
- Using the 5 micron filter provided, instil the AmBisome® preparation into a sterile container with the correct volume of dextrose injection.

**Name :** Miltefosine (Impavido®)

**Class:** Phosphocholine analogue.

**Mechanism of action:** interferes with the synthesis and metabolism of phospholipids. It may also interfere with the parasite's membrane signal transduction, and glycosylphosphatidylinositol anchor biosynthesis.

**Commercial source:** Paladin labs.

**Product appearance:** comes as 10mg and 50mg capsules as a pack of 28 or 56 capsules sealed in 4 or 8 aluminium blister stripes, each containing 7 capsules.

**Administration:** oral, at a dose of 2.5mg/ kg daily for 28 days. For miltefosine, there are no known interactions with other commonly used medications, though this cannot be excluded.

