| Background Information and Trial Rationale | 
Co-infection of human immunodeficiency virus (HIV) and visceral leishmaniasis (VL) was described extensively in the Mediterranean area where an increase of VL cases was noted in HIV-infected individuals in the 1980s. The most important features of co-infection include poor outcome, increased drug toxicity and relapse after treatment with the need for maintenance therapy. The risk of death from VL is nine times higher in those who are co-infected with HIV. In addition there is high parasitaemia with increased potential for transmission.
 
The incidence of cases in the Mediterranean area has decreased with the introduction of highly active anti-retroviral therapy (HAART); however, with further spread of HIV in VL endemic areas, an increase in co-infected cases has been reported in Africa (Ethiopia) and Latin America (Brazil).
 
There are few treatment studies in co-infected patients. In the Mediterranean area, high dose AmBisome® (40 mg/kg total dose) is considered the best treatment option and this is the current formal WHO recommendation.
 
According to the Ethiopian National Guidelines (2006), Sodium Stibogluconate (SSG) and amphotericin B deoxycholate are the first and second line treatments for VL respectively. There are no specific recommendations for HIV-VL co-infected patients. Studies from Ethiopia in co-infected patients however have shown that treatment with SSG has considerable toxicity (mainly pancreatitis) with increased risk of death (odds ratio=6). Miltefosine is better tolerated but has a low cure rate (60% at 6 months). AmBisome® is not routinely available except in special programmes.
 
Recent experience of Médecins Sans Frontières (MSF) in Ethiopia (Abdurafi centre) shows initial cure rates of 74% with AmBisome® 30 mg/kg total dose in 116 patients with a first episode of VL, and only 60% overall in first episode and relapse patients (n=195) of VL with HIV co-infection. Compassionate management of such difficult cases has also included combination treatment of AmBisome® (30 mg/kg total dose) with miltefosine (2.5 mg/kg daily for 28 days) with promising initial results.
 
It should be noted that a preclinical study (unpublished) has also been conducted by DNDi where no major safety interactions were noted between the combination of AmBisome® and miltefosine. Activity enhancement (synergy) has also been noted between the two drugs in another preclinical study. The combination has also been used successfully to treat immunocompetent VL patients in lower doses in phase II and III studies in India.
 
There is little information from other endemic areas; experience from a number of centres in the state of São Paulo, Brazil seem to give similar low cure rates with AmBisome® monotherapy at 21 mg/kg total dose in co-infected patients.
 
This protocol will evaluate the efficacy and safety of the combination of AmBisome® 30 mg/kg with miltefosine (2.5 mg/kg for 28 days) and AmBisome® monotherapy (high dose: 40 mg/kg) in Ethiopia.
 |

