| Test Drugs | 
AmBisome®
This is a liposomal formulation of amphotericin B deoxycholate manufactured and supplied by Gilead Sciences, USA. Each box of AmBisome® is supplied as a pack of 10 vials each containing 50 mg of lyophilised AmBisome®.
AmBisome® must be used according to the manufacturer's instructions.
 
Dosing schedule:
 
AmBisome® monotherapy:
 

Adapted from WHO recommendations for co-infected patients:
40 mg/kg total dose: IV infusion of 5 mg/kg on day 1-5, 10, 17, 24.

 
AmBisome® in combination with Miltefosine:
 

AmBisome®: 30 mg/kg total dose: IV infusion 5 mg/kg on day 1, 3, 5, 7, 9, 11.

Miltefosine: every day during 28 days.
The dose is calculated according to the patient weight:

≤ 25 Kg, the patient receives 50mg (i.e. 1 x 50mg capsule) per day.

> 25 Kg, the patient receives 100mg (i.e. 2 x 50mg capsules) per day.

 |
|-------------------|---------------------------------------------------------------------------------------------------------------------------------------------------------------------------------------------------------------------------------------------------------------------------------------------------------------------------------------------------------------------------------------------------------------------------------------------------------------------------------------------------------------------------------------------------------------------------------------------------------------------------------------------------------------------------------------------------------------------------------------------------------------------------------------------------------------------------------------------------------------------------------------------------------------------------------------------------------------------------------------------------------------------------------------------------------------------------------------------------------------------------------------------------------------------------------------------------------------------------|

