### 4.1. Inclusion criteria

Subjects must meet **all** of the following inclusion criteria to be eligible for enrollment into the study:

- Confirmed HIV positive test (2 rapid diagnostics tests (RDTs) performed in parallel followed by a confirmatory ELISA test).
- Diagnosis of VL (first episode or relapse) confirmed by bone marrow or spleen aspirate.\*
- Male and female age: 18-60 years.
- Written informed consent from the patient.\*\*

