#### AmBisome® in combination with Miltefosine:

- AmBisome®: 30 mg/kg total dose: IV infusion 5 mg/kg on day 1, 3, 5, 7, 9, 11.
- Miltefosine: every day during 28 days.  
The dose is calculated according to the patient weight:
  - ≤ 25 Kg, the patient receives 50mg (i.e. 1 x 50mg capsule) per day.
  - > 25Kg, the patient receives 100mg (i.e. 2 x 50mg capsules) per day.

Miltefosine capsules should be taken with meals.

Dosages of 2 capsules per day should be divided into 2 individual doses to be taken in the morning and evening. In the event the patient vomits within 1 hour of a dose, that dose should be repeated. In the event of repeated vomiting the patient should be withdrawn from that treatment allocation and treated with rescue medication.

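### Miltefosine has two unreconciled dosing rules, 2.5 mg/kg daily and fixed 50/100 mg weight bands, which give different doses at most adult weights

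*Protocol*

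**What the plan says.** The protocol states the miltefosine dose of the combination arm in four current places.

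- **Section 7.1, miltefosine, Administration:** "oral, at a dose of 2.5mg/ kg daily for 28 days". The product description just above it says that the drug "comes as 10mg and 50mg capsules".
- **Section 7.2, dosing schedule:** "≤ 25 Kg, the patient receives 50mg (i.e. 1 x 50mg capsule) per day" and "> 25Kg, the patient receives 100mg (i.e. 2 x 50mg capsules) per day".
- **Synopsis, Background Information and Trial Rationale:** the closing sentence says what the trial will evaluate, namely AmBisome 30 mg/kg "with miltefosine (2.5 mg/kg for 28 days) and AmBisome" monotherapy at 40 mg/kg.
- **Synopsis, Test Drugs:** "The dose is calculated according to the patient weight", followed by the same two bands as in Section 7.2.

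The 28-day duration is the same in all four. The synopsis therefore carries both rules, one in its rationale and the other in its Test Drugs row. The primary objective and the arm definitions in the Section 1 Rationale give no miltefosine amount, so they do not settle the matter. Eligibility is "Male and female age: 18-60 years" with no weight limit, and no expected weight distribution is given.

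**The concern.** A dose proportional to weight and a fixed dose within a band are different instructions. Nothing in the protocol calls 2.5 mg/kg a nominal figure, calls the bands an approximation of it, or sets an order of precedence.

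Miltefosine is what the combination arm adds to AmBisome 30 mg/kg, and the Section 1 Rationale judges that AmBisome dose on its own to have too low an efficacy. The arm is then tested by itself against a 75% cure rate, and the result decides whether the regimen can be considered for compassionate use. A regimen judged in that way needs one definition. Two things are at stake:

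- **Dose given.** Staff following Section 7.1 and staff following Section 7.2 could give the same patient different daily amounts. Section 9.1, which has treatment resumed after a short interruption until the full dose has been given, also depends on which rule defines the full dose.
- **Description of the regimen.** If Section 7.2 is followed, a report that repeats the synopsis rationale would state a mg/kg dose that patients away from about 40 kg did not receive.

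**Working it through.** **Inputs from the protocol.** Section 7.1: 2.5 mg/kg/day. Section 7.2: 50 mg/day for weight w ≤ 25 kg, and 100 mg/day for w > 25 kg.

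**Assumption.** Body weight. The protocol gives none, so a range is shown, mainly 30 to 70 kg since only adults are enrolled.

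**Formulas.**
- mg/kg rule: 2.5 × w mg/day.
- Band rule: 50 mg/day if w ≤ 25 kg, 100 mg/day if w > 25 kg.
- Delivered mg/kg under the bands: band dose / w.
- Relative difference: band dose / (2.5 × w) − 1. Above 25 kg this is 40/w − 1.

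**Where the stated 2.5 mg/kg is reproduced.** In the lower band, 50 / 2.5 = 20 kg. In the upper band, 100 / 2.5 = 40 kg. The rules agree at no other weight.

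**Where they are close.** Above 25 kg, a difference of at most 10% needs 40/w between 0.9 and 1.1, so w runs from 100 / (2.5 × 1.1) = 36.4 kg to 100 / (2.5 × 0.9) = 44.4 kg.

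| Weight (kg) | Bands (mg/day) | 2.5 mg/kg (mg/day) | mg/kg under bands | Bands relative to 2.5 mg/kg |
|---|---|---|---|---|
| 30 | 100 | 75 | 3.33 | +33% |
| 35 | 100 | 87.5 | 2.86 | +14% |
| 40 | 100 | 100 | 2.50 | 0% |
| 45 | 100 | 112.5 | 2.22 | −11% |
| 50 | 100 | 125 | 2.00 | −20% |
| 55 | 100 | 137.5 | 1.82 | −27% |
| 60 | 100 | 150 | 1.67 | −33% |
| 70 | 100 | 175 | 1.43 | −43% |

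**Over the 28-day course.** At 50 kg: 28 × 100 = 2800 mg against 28 × 125 = 3500 mg. At 60 kg: 2800 mg against 28 × 150 = 4200 mg.

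**Comparison with the other drug.** The AmBisome schedules reproduce their stated totals: 8 infusions × 5 mg/kg = 40 mg/kg and 6 × 5 mg/kg = 30 mg/kg. The mismatch is confined to miltefosine.

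**The case against.** The best defence is that the operative rule can be recognised. Section 7.2 is the section on doses and regimens, it counts capsules and explains how to split two of them over the day, and the synopsis Test Drugs row repeats it. Section 7.1 mainly describes the products, and its AmBisome entry gives preparation steps without a mg/kg dose. On that reading 2.5 mg/kg is a nominal label and the bands are the instruction. This is plausible, and it makes uniform use of Section 7.2 likely. It remains an inference: the 2.5 mg/kg figure stands under Administration as a dose, and no sentence subordinates it. If the inference is right, the synopsis rationale still names a dose that the bands do not deliver at most of the weights shown.

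Several stronger readings are tempting, but the documents do not support them.

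- **That the two sites will dose differently.** This is a risk and is not shown. The 10 mg capsules appear in a description of the product, and nothing says that they are supplied to the sites.
- **That the synopsis regimen is simply not the one given.** The synopsis Test Drugs row matches Section 7.2. The synopsis is inconsistent within itself.
- **That the trial is bound to report a wrong mg/kg conclusion.** The objectives, the arm definitions and the title of the combination-arm pharmacokinetic schedule name no miltefosine mg/kg. Only the synopsis rationale does so for the regimen under test.
- **That miltefosine levels could not be related to dose.** Weight is measured at screening and at visits (Section 8.3), oral doses are directly observed (Section 10.5), and dose changes go on the case report form (Section 8.7.3). Delivered mg/kg can be derived.
- **That the bands are themselves wrong,** because the dose doubles just above 25 kg or because there is no higher band. Those are features of the band rule. They are not contradictions, and this point takes no view on them.

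**Conclusion.** The contradiction stands. Two places give 2.5 mg/kg daily, two give fixed 50/100 mg bands, and nothing links them. The rules agree exactly only at 20 and 40 kg and, above 25 kg, are within 10% only from about 36 to 44 kg. Elsewhere in the range shown the bands run from 33% above the mg/kg dose at 30 kg to 33% below it at 60 kg and 43% below at 70 kg.

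The arithmetic is exact at each weight. How many patients are affected, and by how much, depends on a weight distribution that the protocol does not give. The practical consequence is conditional: a patient well away from 40 kg could receive a different dose depending on the section followed, and if Section 7.2 is followed the label 2.5 mg/kg misstates the dose. The primary endpoint, stopping boundaries, error rates and maximum of 66 patients per arm are not affected. The point should still be corrected, because it concerns the dose of an investigational drug and the definition of the regimen being tested.

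**What to change.** Reconcile Section 7.1 (Administration), Section 7.2, the synopsis rationale and the synopsis Test Drugs row so that one miltefosine dosing rule stands throughout. If the mg/kg figure is meant only as a nominal description of the bands, say so wherever it appears. Describe the tested regimen in the terms of the chosen rule. The choice belongs to the sponsor and investigators.

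As an option, summarise the delivered mg/kg in the combination arm from the weight and dosing records already planned.

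The cost is a wording amendment in four places, with the usual approvals, and at most one derived variable. No extra patients, visits or samples are needed.
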